#### Data collection

Data will be extracted from the TIER.Net database (as an MS Excel export file). TIER.Net captures demographic information such as patient age, sex, facility name and contact details and also HIV specific information such as HIV diagnosis date, ART start date, regimen at baseline, ART visit dates, CD4 count, viral load done and viral load suppression The system also records all treatment related information, including ART switch. All these variables will be extracted (see S1 Appendix study codebook). The data will be exported to STATA 15.1 for data cleaning and analysis. Records with missing data will be excluded in the final analysis. This will be after conducting all necessary data quality checks, verifications, and triangulations with other data sources.

*Outcome*. VL count is categorized into suppressed (<1000 copies/ml) or unsuppressed (**≥**1000 copies/ml) [48,49]. The status on retention in care for patients will be categorized into active in care, LTFU, transferred out, or recorded dead. For this study, LTFU is defined as having missed a scheduled medical appointment by 90 days or more, as defined by the South African Department of Health [50].

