#### Data analysis

Data will be coded and analysed using STATA version 15.1. Tests of association (Chi-square and t-test) between outcome variables and selected demographics characteristics and clinic indicators will be conducted. Outcome variables will include viral load detectability and retention outcomes (active in care, transferred-out, lost to follow-up and dead),. Regression analysis, univariate and multivariate analyses between variables will be built for outcome variables to identify independent predictors. Variables such as age, sex, health facility, baseline regimen, ART start date, baseline CD4 count, most recent CD4 count, ART visit dates, and months on ART will be considered as predictor variables or independent variables. Analysis will include survival analysis which will consider different entry time points into the ART program. Subsequently, patients will not be grouped all together but will be followed up in a 12-month interval when measuring the outcomes (virological failure and lost to follow up).

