### Data management/Data cleaning (phase I-IV)

Data quality scripts for phase I, II, IV will be written in STATA. Data quality checks for phases I, II, and IV (quantitative data) will be done through RedCap (a secure web platform for building and managing research databases). Since TIER.Net will be used as the primary data source for phase I data extraction in the city of Johannesburg region F, where there are data quality issues, the study team will liaise with the facility staff and developmental partners in the region to assist with data clean-up activities. Data quality issues with the ITREMA data (phase II) will be communicated to the ITREMA study quality assurance officer for rectifying. Data quality checks for phase III (qualitative data) will be done in Microsoft Word (before exporting data to NVIVO). All transcripts will be checked for completeness and accuracy against original interviews. Creditability of data analysis will be ensured through triangulation of data sources (i.e., original interviews, field notes, transcripts, medical record).

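### In Phase I, deaths not recorded in TIER.Net count as loss to follow-up, so associations of LTFU with CD4 and age may partly reflect mortality and should not be read as disengagement alone

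*Protocol article*

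**What the plan says.** The Outcome paragraph under Phase I, Data collection, sets four retention states: "The status on retention in care for patients will be categorized into active in care, LTFU, transferred out, or recorded dead". It then fixes the rule for one of them: "LTFU is defined as having missed a scheduled medical appointment by 90 days or more", citing the South African Department of Health. Vital status plays no part in that rule.

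The Phase I Data analysis section lists the same four states as outcome variables and plans regression models for the outcomes, to identify independent predictors. Age is among the candidates, and so is CD4: "baseline CD4 count, most recent CD4 count, ART visit dates, and months on ART will be considered as predictor variables". The survival analysis names virological failure and LTFU as its outcomes.

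Two statements bear on data quality. Records with missing data are excluded, and of this step the article says: "This will be after conducting all necessary data quality checks, verifications, and triangulations with other data sources". The data management section adds that, where there are problems with TIER.Net data, "the study team will liaise with the facility staff and developmental partners in the region to assist with data clean-up activities". Neither statement names a source for deaths. The limitations mention inconsistent and missing secondary data in general, but not deaths classed as LTFU.

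**The concern.** A patient who dies without the death being entered in TIER.Net stops attending. Once the next appointment is 90 days overdue, that patient meets the LTFU rule. The LTFU category then holds two groups: people who stopped attending and people who died unrecorded.

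This misclassification is unlikely to be even across predictor levels. If low CD4 or older age raises the risk of death, those patients contribute more unrecorded deaths to LTFU. Covariate adjustment does not remove the bias, because the outcome itself is misclassified.

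What is at stake is interpretation. The overarching hypothesis is that the study will identify barriers and facilitators to adherence and retention, in order to strengthen adherence interventions. A CD4 or age association produced partly by death could be taken as evidence about who disengages. With about 130 000 records, even a small bias of this kind could be statistically significant.

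**Working it through.** The article gives no figure to reproduce: 130 000 is a count of records, not a calculated sample size. The check is therefore a misclassification calculation under stated assumptions.

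**Inputs**
- From the article: the LTFU rule, the four retention states, CD4 as a predictor, about 130 000 adults.
- Assumed: L, the true risk of disengaging, is 10%, 20% or 30% and equal in both CD4 groups, so the true risk ratio is 1. The death risk d at higher v low CD4 is 2% v 6%, 2% v 10% or 5% v 15%. The share u of deaths not recorded is 10%, 30% or 50%. For significance, 30% of patients have low CD4.

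**Formula**

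Observed LTFU risk = L + u × d, so observed RR = (L + u × d_low) / (L + u × d_high).

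Worked case, L = 20%, deaths 2% v 10%, u = 50%: low CD4 0.20 + 0.5 × 0.10 = 0.25; higher CD4 0.20 + 0.5 × 0.02 = 0.21; RR = 0.25 / 0.21 = 1.19.

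**Spurious RR for low CD4 (true RR = 1)**

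| L | Deaths, higher v low CD4 | u = 10% | u = 30% | u = 50% |
|---|---|---|---|---|
| 10% | 2% v 6% | 1.04 | 1.11 | 1.18 |
| 10% | 2% v 10% | 1.08 | 1.23 | 1.36 |
| 10% | 5% v 15% | 1.10 | 1.26 | 1.40 |
| 20% | 2% v 6% | 1.02 | 1.06 | 1.10 |
| 20% | 2% v 10% | 1.04 | 1.12 | 1.19 |
| 20% | 5% v 15% | 1.05 | 1.14 | 1.22 |
| 30% | 2% v 6% | 1.01 | 1.04 | 1.06 |
| 30% | 2% v 10% | 1.03 | 1.08 | 1.13 |
| 30% | 5% v 15% | 1.03 | 1.10 | 1.15 |

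Across these cases unrecorded deaths make up about 1% to 29% of apparent LTFU.

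**Chance of a significant result.** With all 130 000 records pooled and two-sided alpha 0.05, the spurious association is significant with probability 30% to nearly 100% at u = 10%, and at least 99% at u = 30% or more. Excluding incomplete records or splitting the cohort would lower these figures.

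**If low CD4 truly protects.** Take a true RR of 0.80 (16% v 20%) and deaths 10% v 2%. Observed RR = (0.16 + 0.10u) / (0.20 + 0.02u):
- u = 10%: 0.170 / 0.202 = 0.84
- u = 30%: 0.190 / 0.206 = 0.92
- u = 50%: 0.210 / 0.210 = 1.00

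Here the bias hides an effect and creates no risk factor.

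**What a composite can and cannot do.** Attrition risk = L + d, which does not contain u. With L = 20% and deaths 10% v 2% it is 30% v 22%, RR 1.36, whatever share of deaths is recorded. It is robust to recording, but it includes all the mortality and so cannot show whether CD4 acts on disengagement.

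**The case against.** The strongest reply is that nothing in the article is contradictory. LTFU follows a declared national definition, the label of the death category shows that only recorded deaths are meant, and Objective 1 asks about LTFU. That stands: the definition is legitimate and need not change. The point concerns what may be concluded from its predictors.

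A reader might infer that the plan has no analysis able to reveal the problem. The article does not support that. Death is one of the listed outcomes, and models are planned for the outcomes, so the study can show whether low CD4 or older age predicts recorded death. This would warn the analyst, but it does not show how much of the LTFU association comes from unrecorded deaths.

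A reader might also infer that low CD4 is bound to emerge as a predictor of LTFU. That too is unsupported. It depends on the mortality gradient, the share of deaths unrecorded and the true relation between CD4 and disengagement, and the article gives none of them. The protective example shows the opposite pattern.

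The promised triangulation and clean-up may recover some deaths, and an article need not name every source or sensitivity analysis. This is a fair limit on the criticism, but not an answer to it. The bias follows from a rule that the article does state, and the safeguards as described are not directed at deaths.

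Finally, recommendations draw on all four phases, so a misreading of Phase I would not by itself decide where adherence support goes.

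**Conclusion.** The point holds in a limited form. Under the Phase I definitions, a death not recorded in TIER.Net is classed as LTFU unless triangulation captures it. Associations of LTFU with markers of mortality may therefore be inflated, or a protective effect masked, and should not be read as disengagement alone.

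The direction of the bias for low CD4 follows from the definitions, provided that low CD4 raises mortality and recording is no more complete in that group. Its size is unknown. The risk ratios in the table are illustrations that rest wholly on assumed risks; they are not estimates for this cohort. At the lower end the bias is trivial in size, although the large cohort could still make it significant.

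**What to change.** 1. Keep the Department of Health definition of LTFU. State which source, if any, the triangulation uses for deaths, and list unrecorded death as a limitation.
2. Report attrition (LTFU or recorded death) alongside LTFU and recorded death, with the same predictors. Present it as a composite whose status is robust to death recording, not as a test of disengagement. In the survival analysis its timing still depends on recording, since an unrecorded death is dated by the missed appointment.
3. Add a sensitivity analysis that reassigns part of LTFU to death over a range fixed in advance, for example equivalent to 10% to 50% of deaths unrecorded, weighted to low CD4 and older age. One way is to anchor it on recorded deaths within CD4 and age groups: if a share u is unrecorded, the number to reassign is recorded deaths × u / (1 − u), which is 0.11, 0.43 and 1.00 times recorded deaths at u = 10%, 30% and 50%. In the example with L = 20%, deaths 10% v 2% and u = 30%, recorded deaths are 7.0% v 1.4%. Reassigning 3.0% v 0.6% takes observed LTFU from 23.0% v 20.6% back to 20.0% in both groups.
4. Interpret CD4 or age as predictors of disengagement only if the LTFU association persists across the whole range.

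The cost is one extra outcome and one sensitivity analysis on data already to be extracted. Fewer predictors may be reported as specific to LTFU, and the reassigned shares remain assumptions.

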#### Data analysis

Data will be coded and analysed using STATA version 15.1. Tests of association (Chi-square and t-test) between outcome variables and selected demographics characteristics and clinic indicators will be conducted. Outcome variables will include viral load detectability and retention outcomes (active in care, transferred-out, lost to follow-up and dead),. Regression analysis, univariate and multivariate analyses between variables will be built for outcome variables to identify independent predictors. Variables such as age, sex, health facility, baseline regimen, ART start date, baseline CD4 count, most recent CD4 count, ART visit dates, and months on ART will be considered as predictor variables or independent variables. Analysis will include survival analysis which will consider different entry time points into the ART program. Subsequently, patients will not be grouped all together but will be followed up in a 12-month interval when measuring the outcomes (virological failure and lost to follow up).

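### Phase I lists months on ART, ART visit dates and most recent CD4 as candidate predictors without dating them before the outcome: a problem for loss to follow-up with all three, and for virological failure with most recent CD4 only

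*Protocol article*

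**What the plan says.** All references are to the Protocol article, Materials and methods: Phase I.

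- **Predictors (Data analysis).** The list opens with "Variables such as age, sex, health facility, baseline regimen, ART start date" and continues: "baseline CD4 count, most recent CD4 count, ART visit dates, and months on ART will be considered as predictor variables or independent variables". Baseline and later-measured variables stand side by side, and no measurement date is given for the later ones.
- **Purpose (Data analysis).** Univariate and multivariate regression models "will be built for outcome variables to identify independent predictors".
- **Outcomes (Data analysis).** "Outcome variables will include viral load detectability and retention outcomes", the latter being active in care, transferred out, LTFU and dead.
- **Outcome definitions (Data collection, Outcome).** "LTFU is defined as having missed a scheduled medical appointment by 90 days or more". Viral load is split at 1000 copies/ml.
- **Time structure (Data analysis).** "Analysis will include survival analysis which will consider different entry time points into the ART program". The next sentence says that patients will not be pooled but followed in 12-month intervals. It ties those intervals to the measurement of virological failure and LTFU and does not say when predictors are taken.

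**The concern.** A predictor should be known before the outcome it is meant to predict. Three listed variables need not be.

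- **ART visit dates.** LTFU is read off missed appointments, so attendance dates are an ingredient of the outcome. Using them to predict it is circular.
- **Months on ART.** If counted to last visit or exit, LTFU itself shortens it. ART start date is in the same list, and start date plus months on ART is then the exit date, which nearly or fully shows who left. If counted to extraction for everyone, it is exactly collinear with ART start date.
- **Most recent CD4.** In a patient who left, the series stops at disengagement. In a retained patient it continues to be updated while CD4 recovers on treatment, so the last value partly measures length of follow-up. For virological failure, a last CD4 taken at or after viraemia may be lowered by it.

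Objective 1 of Phase I is to assess which demographic and clinical indicators are associated with virological failure and LTFU. With about 130 000 records, an artefact of this kind would carry a very narrow confidence interval and would also distort the coefficients of the genuine baseline variables in the same model.

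**Working it through.** Phase I states no power, alpha, LTFU rate or CD4 trajectory, so there is no figure in the plan to reproduce. The mechanism was checked by simulation with every true effect set to zero.

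**Inputs from the article.** ART start between 1 April 2004 and 29 February 2020 (191 months); at least 12 months of follow-up; the predictor list above.

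**Assumptions.** Uniform entry; database closure 12 months after the last entry (191 + 12 = 203 months from the origin); exponential LTFU at 5, 10 or 20 per 100 person-years, independent of all covariates; CD4 rising by up to 300 cells on ART; 20 000 patients (4 000 for the Cox fits). Deaths and transfers were not simulated.

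**1. Months on ART accrued to exit, logistic model for LTFU**

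| Assumed LTFU per 100 person-years | Mean months, LTFU / not LTFU | OR per year on ART | z |
|---|---|---|---|
| 5 | 60.0 / 95.3 | 0.85 | -41.9 |
| 10 | 50.6 / 82.3 | 0.84 | -43.3 |
| 20 | 38.8 / 62.7 | 0.84 | -35.9 |

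The true OR is 1.

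**2. Months on ART together with ART start date.** Start + months = exit date. If active patients' months run to closure, the sum is 203 for every retained patient and below 203 for every LTFU patient. Separation is complete and no finite maximum-likelihood estimate exists. If months run to the last visit, active patients' sums fall short of closure and overlap with those of LTFU patients. A check with the 90-day rule and assumed appointment gaps of 28/56/84 or 28/84/168 days still gave an AUC above 0.999.

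**3. Within one 12-month interval.** If months are counted to the end of the interval, every LTFU patient has fewer than 12 and every retained patient has 12. The interval alone does not help.

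**4. Most recent CD4 and LTFU, per 100 cells**

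| Assumed LTFU per 100 person-years | Logistic OR, adjusted for baseline CD4 and start date | Cox HR, adjusted for baseline CD4 |
|---|---|---|
| 5 | 0.30 | 0.24 |
| 10 | 0.27 | 0.25 |
| 20 | 0.24 | 0.27 |

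The true values are 1. Survival analysis does not remove the artefact, because a patient must stay longer to acquire a later, higher CD4.

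**5. Predictors fixed at the start of each 12-month interval**

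| Assumed LTFU per 100 person-years | Months on ART, OR per year | CD4 at interval start, OR per 100 cells |
|---|---|---|
| 5 | 1.000 | 1.013 |
| 10 | 0.999 | 0.992 |
| 20 | 1.005 | 0.979 |

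The largest |z| is 1.0 for months and 1.7 for CD4. The false associations disappear.

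**6. Virological failure.** With failure assigned independently of time on ART (assumed 20%), months on ART at the viral load date gives OR 0.999 per year (z -0.2), so there is no artefact. For CD4, assume SD 180 and a fall of d cells caused by failure. For equal-variance normal groups, the log OR per 100 cells is -100d/180²:

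- d = 25: -2500/32 400 = -0.077, OR 0.93
- d = 50: -5000/32 400 = -0.154, OR 0.86
- d = 100: -10 000/32 400 = -0.309, OR 0.73

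Simulation gave 0.93, 0.86 and 0.74. Here CD4 is only a consequence of failure, yet it appears as a predictor.

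**The case against.** The strongest defence is that the same paragraph plans survival analysis with differing entry times and 12-month intervals. Start date, visit dates and months on ART are the raw inputs for such a time axis. The list gives candidates ("most recent CD4 count, ART visit dates, and months on ART will be considered as predictor variables or independent variables"), and the article refers to a study codebook, not shown here, that may define each variable. The pooled logistic figures in steps 1 and 2 also describe a model that the interval sentence seems meant to avoid. The last point stands: those figures show a direction and a mechanism, not a forecast. The rest does not clear the text. The intervals are specified for outcomes only, steps 3 and 4 show that intervals or a Cox model alone leave the artefact in place, and visit dates are named outright as a predictor.

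A reader might infer more than the article supports, in four ways:

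- **That all three variables are equally faulty for virological failure.** They are not. A viral load of 1000 copies/ml or more determines neither visit dates nor months on ART, and only most recent CD4 is open to reverse causation.
- **That retention status would be predicted perfectly.** That depends on how months on ART is defined. Under the last-visit reading, separation is near, not exact.
- **That artefacts will certainly be reported.** The variables are only to be considered, and dating them at interval start would remove the problem.
- **That only baseline covariates are admissible.** Lagged or time-updated values are legitimate.

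**Conclusion.** The point holds for LTFU with all three variables, and for virological failure with most recent CD4 alone. It concerns a stated analysis choice, not a detail left to another document: the article names these variables as predictors, and the planned survival analysis and intervals govern outcome measurement only. As written, the models could present artefacts as independent predictors.

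In the null simulations the LTFU artefact appeared at every assumed rate, with odds ratios near 0.84 per year on ART and hazard ratios near 0.25 per 100 cells of most recent CD4. Those sizes rest on the assumed LTFU rates, closure date and CD4 trajectory, and the virological failure figures rest on the assumed CD4 fall. They should not be read as predictions for this cohort. That an LTFU artefact arises when months on ART and CD4 are taken up to exit does not depend on the assumed rate.

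**What to change.** Amend the predictor list in Phase I, Data analysis, so that each predictor is dated before the outcome:

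- Use ART visit dates only to derive outcomes and intervals, and delete them as a predictor.
- Make time since ART start the time axis of the LTFU survival model, or enter months on ART only as its value at the start of each 12-month interval.
- Replace most recent CD4 by the latest CD4 recorded before the start of the interval or, in the viral load model, before the viral load date.
- In the viral load model, use time on ART at the date of that viral load.
- Keep the baseline covariates, and keep ART start date as calendar year of start.

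The cost is wording and model specification. The variables are already to be extracted from TIER.Net. The one loss is that most recent CD4 at extraction can no longer be reported as a predictor.

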### Materials and methods: Phase II

Objective 2: Assess socio-demographic and psychosocial associated with adherence (self-reported adherence, pill count and virological failure) in patients on first line and second-line ART in a rural community.

#### Study design

This cohort study using secondary data analysis will be conducted as a sub-study of the Intensified Treatment Monitoring Accumulation (ITREMA) study (Clinicaltrials.gov Identifier NCT03357588) [51]. The ITREMA database will be used to extract ART information. ITREMA is an open-label randomised clinical trial evaluating different treatment monitoring strategies for first-line ART, which ran from June 2015 to January 2019 [51]. ITREMA was conducted at the Ndlovu medical centre in Limpopo province, South Africa. The ITREMA study enrolled adult PLHIV and assessed an intensified HIV-treatment monitoring strategy in a randomised comparison with a control group receiving standard-of-care HIV treatment in accordance with the South Africa National Department of Health guidelines

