### Research questions and hypotheses

What are the demographic characteristics and clinical indicators associated with virological failure and being lost to follow-up (LTFU) in PLHIV taking first-line and second-line ART in urban communities?Hypothesis: Demographic and clinical characteristics are associated with virological failure and being LTFU in patients on ART from complex, and highly mobile urban communities.What are the intra-and inter-personal factors (demographic, socio-economic characteristics), social and community level factors (poverty, social norms, HIV related stigma, culture), structural factors (health systems, support services) and clinical indicators associated with self reported adherence, pill count and virological failure to first-line and second-line ART in rural communities?Hypothesis: Individual and community level factors are associated with self-reported non-adherence, suboptimal pill count, and virological failure in patients on ART in the rural setting.What are the perspectives of virally suppressed and unsuppressed first-line and second-line ART patients about treatment adherence in selected urban and rural communities?
Are there any differences between people receiving first-line and second-line ART?Are there any differences in treatment taking behaviours between virally suppressed and unsuppressed ART patients?What do virally suppressed and unsuppressed ART patients recommend as adherence strategies?Hypothesis: In South African communities, treatment taking behaviour, perceptions of adherence, and recommendations for adherence interventions differ between PLHIV who are virally unsuppressed and those who are virally suppressed.What treatment adherence strategies and interventions have been implemented and evaluated in sub-Saharan Africa for HIV, hypertension, and DM?Hypothesis: There are no differences in the effectiveness of adherence interventions implemented in sub-Saharan Africa for HIV, hypertension, and DM.

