### Materials and methods: Phase I

Objective 1: Assess demographic characteristics and clinical indicators associated with virological failure and LTFU in first-line and second-line patients in an urban community.

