#### Sampling/Sample size

All the records from ITREMA database will be used. There are 501 ART patients in the ITREMA database.

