#### Data analysis

Data will be coded and analysed using STATA version 15.1. Tests of association (Chi-square and t-test) between outcome variables and selected socio-demographics and health related characteristics will be conducted. Outcome variables will include (but not limited to) viral load detectability, retention outcomes (active in care, transferred-out, lost to follow-up and dead), side effects and treatment interruptions (stop and restarting treatment). Regression analysis, univariate and multivariate analyses between variables will be built for outcome variables to identify independent predictors. Variables such as age, sex, health facility, beliefs, education, economic status, employment status, religious status, disclosure, and months on ART will be considered as predictor variables or independent variables.

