#### Sampling/Sample size

In this study, purposive sampling of patients currently taking ART will be employed to ensure maximum variation among the study sample. We will ensure a diverse sample by considering viral load status (suppressed and unsuppressed time on ART, age (18 years and older), sex (both males and females) and education. Sample size will depend on when saturation is reached; we anticipate that a maximum of 60 IDIs will be conducted across both study settings and viral load status groups (suppressed and unsuppressed). An anticipated number of study participants to recruit is 15 per viral load status group in each study setting (making a total of 30 participants in each study setting).

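### Phases II and III are not set up to answer their first-line/second-line questions: the rural data come from a first-line trial, and the interviews are not sampled on treatment line

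*Protocol article*

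**What the plan says.** **Phase II.** The second research question and Objective 2 both cover the two treatment lines; the objective concerns adherence "in patients on first line and second-line ART in a rural community". The only data source is the ITREMA database. The Phase II study design section says: "ITREMA is an open-label randomised clinical trial evaluating different treatment monitoring strategies for first-line ART". The sample size section says: "There are 501 ART patients in the ITREMA database". It gives no split by line. The data analysis section lists candidate predictors: "Variables such as age, sex, health facility, beliefs, education, economic status, employment status, religious status, disclosure, and months on ART will be considered". Neither treatment line nor regimen is among those named, although the list is open.

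**Phase III.** Under the third research question the article asks: "Are there any differences between people receiving first-line and second-line ART". Objective 3 also names both lines. On sampling, the article says: "We will ensure a diverse sample by considering viral load status", and continues with time on ART, age, sex and education. Target numbers are 15 interviews per viral load group in each setting, up to 60 overall. The Phase III study design section says that interviewees will be active patients from Phases I and II.

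**The concern.** The study's aim covers adherence on both first-line and second-line ART, and the phases are to be merged into one set of recommendations. Two of them do not secure the second-line half of that aim.

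In Phase II, a cohort described as a first-line trial cannot be assumed to hold a usable second-line group. Second-line patients who do appear are likely to have been switched during the trial. Virological failure, one of the three Phase II outcomes, is defined as viraemia of at least 1000 copies/ml within 96 weeks. Where failure led to the switch, the patient already has the outcome by the time second-line status begins. Pooling such patients and labelling the result as covering both lines would say nothing reliable about adherence or failure on second-line treatment.

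In Phase III, the comparison of lines is an explicit sub-question, but nothing in the sampling plan ensures enough second-line interviews to address it. Because the rural interviewees come from the ITREMA cohort, the Phase II weakness carries over. If second-line interviewees came only from Johannesburg, a pooled comparison of lines would also mix treatment line with urban versus rural setting. Analysis cannot repair this once recruitment is over.

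**Working it through.** **1. The plan's own interview number.** 15 per viral load group × 2 groups = 30 per setting; 30 × 2 settings = 60. This reproduces the stated maximum. All four cells are defined by viral load and setting, and none by treatment line.

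**2. Question against data source.**

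| Phase | What is asked | What supplies the answer | Second-line provision |
|---|---|---|---|
| II | Factors associated with adherence and failure, both lines, rural | ITREMA, described as a first-line trial, 501 records | No count; line not among named predictors |
| III | Whether first-line and second-line patients differ | Up to 60 interviews; rural frame is the ITREMA cohort | Line not a named criterion; no minimum |

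**3. Order of events in Phase II.** If patients enter on first-line ART, second-line status can arise only through a later switch. If the switch was prompted by failure, the sequence is: first-line ART, failure (the outcome), switch, second-line status. An association between second-line status and failure in that subgroup is then built in by the sequence. The article does not give reasons for switching, so how many patients this affects is unknown.

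**4. Illustrative yield in Phase III.** The documents give no second-line share, so p below is an assumption. The calculation also assumes recruitment that takes no account of line. Formulas: expected number = 60p; chance that a cell of 15 has no second-line patient = (1 − p)^15; chance that the 30 rural interviews contain none = (1 − p)^30; chance of at least 5 among 60 from the binomial distribution.

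| Assumed p | Expected of 60 | None in a cell of 15 | None in 30 rural | At least 5 of 60 |
|---|---|---|---|---|
| 2% | 1.2 | 0.74 | 0.55 | 0.01 |
| 5% | 3 | 0.46 | 0.21 | 0.18 |
| 10% | 6 | 0.21 | 0.04 | 0.73 |
| 20% | 12 | 0.04 | 0.001 | 1.00 |

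For example, at 5%: 60 × 0.05 = 3 and 0.95^15 = 0.46. At 10%: 60 × 0.10 = 6 and 0.90^15 = 0.21.

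**5. The same shares applied to ITREMA.** 501 × 0.02 = 10; 501 × 0.05 = 25; 501 × 0.10 = 50; 501 × 0.20 = 100. The article does not say which, if any, applies.

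**The case against.** The strongest reply has four parts.

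- **Phase II does not compare the lines.** It asks about factors among patients on either line, so a thin second-line group does not make the whole question unanswerable. This stands. The first-line analysis is unaffected; the fault is in claiming second-line coverage.
- **ITREMA's eligibility rules are in a cited source that is not shown.** One descriptive clause cannot prove that nobody was on second-line ART. This also stands, so an absence of second-line patients is not established. The article still states the wider objective without a count to support it.
- **Phase III is purposive and seeks maximum variation.** Recruiters might seek out second-line patients, and half the sample is unsuppressed by design, so an overall clinic share need not apply. Regimen and treatment history are interview topics. This weakens the yield calculation, which is why it is only an illustration. But asking about regimen at interview identifies line after recruitment and does not secure second-line participants.
- **The study is descriptive, with no primary test between lines.** True, but the comparison is one of its own stated sub-questions.

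A reader might infer more than the article supports:

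- **That every phase has this fault.** Phase IV poses no treatment-line question.
- **That Phase I credits second-line time to the starting regimen, or suffers immortal-time bias.** Its objective does cover "virological failure and LTFU in first-line and second-line patients in an urban community", and baseline regimen is the only regimen term named. But the predictor list is open, and of TIER.Net the article says: "The system also records all treatment related information, including ART switch". Those variables will be extracted, so Phase I can address line, and no biased classification is specified.
- **That the introduction's 20–30% first-line failure figure caps second-line numbers in ITREMA** at 501 × 0.20 = 100 to 501 × 0.30 = 150, all of them failures. The figure is national, has no time frame and measures failure rather than switching. The article gives no reasons for switching.

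**Conclusion.** The point holds for Phases II and III. In Phase II, the stated population is wider than the described data source supports, and no second-line count closes the gap. In Phase III, an explicit comparison has no matching sampling criterion or minimum number, and its rural frame inherits the Phase II limitation. The right description is that these phases are not set up to answer the question; the documents do not show that they cannot.

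The size cannot be fixed from the article. An expected 3–6 second-line interviews of 60 at an assumed 5–10% share, or 12 at 20%, shows how sensitive the comparison is to an unstated quantity. It is not a forecast. The Phase II conclusion assumes that ITREMA participants started on first-line ART, as its description implies. The outcome-dependence argument applies only to those switched because of failure.

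**What to change.** **Phase II.** Restate research question 2 and Objective 2 as first-line ART. Alternatively, report how many ITREMA patients were on second-line ART and present them separately and descriptively, not pooled with first-line patients. The count should be available from the database already being extracted.

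**Phase III.** Add treatment line to the purposive criteria, with a minimum number of second-line interviews per setting within the same 60. If second-line patients are not available at the rural site, drop the line comparison there and say that it rests on the urban facilities. This must be settled before recruitment.

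**Cost.** Changes of wording, one count and a sampling quota, with no extra interviews. The downside is that the rural claim may narrow to first-line ART and recruitment becomes slightly more constrained.
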